#### Monthly check-ins

Participants receive monthly SMS prompts or emails (based on participant preference) that will query employment, earnings, and service needs for psychological counseling or SRH. The check-ins promote both engagement and retention of the cohort and provide an immediate, targeted, and relevant response or referral to services at or near when participants experience distress or needs. Like surveys, check-in links are sent up to four times. To support compliance, participants are provided $100 for responding to at least 80% of the monthly prompts sent. Finally, the team also sends monthly text messages to remind participants about financial capability program opportunities or to let participants know about upcoming events, such as job fairs.

#### Monitoring intervention uptake

Uptake of financial capability options are monitored via electronic reporting forms, entered into a Salesforce database, which is used to record attendance at peer discussion groups and mentoring sessions using participant ID, date, and activities completed. We monitor GI payments via the CFR card to ensure monthly payments were disbursed. We continually examine intervention activity and project milestones to assess observed vs. expected enrollments, uptake, and continuation of activities, with pre-specified timepoints for comparison and decision making. For example, should we find that fewer than 40% of enrolled participants are engaging in the peer discussion groups, this will trigger a review discussion with staff and the CWG to determine if additional recruitment or training efforts are needed, if there are structural barriers lowering attendance that need to be addressed (e.g., childcare needs, night school), and whether some programming should be re-oriented.

#### Qualitative data collection

We conduct three in-depth interviews over a period of 2 years (following enrollment, 12 months and 24 months) with 36 purposively selected participants, for a total of 108 interviews. Potential participants are identified by MyPath staff at enrollment and qualitative researchers select and contact potential participants to balance the sample by “Phase 1 GI” vs. “Phase 2 GI,” residential location (Oakland vs. San Francisco), gender, as well as other emergent criteria based on ongoing data collection (i.e., parenting status). The first interview is conducted within 2 months of enrollment; the second and third interviews will occur 1 and 2 years later, allowing us to capture the period before GI receipt, when GI ends, and a year after GI has ended. The first interview will focus on current living situation, education and employment status; personal and financial aspirations, including personal goals related to GI support; community involvement and support; family relationships; and current practices around physical and mental health, including access and utilization of health services. The second and third interviews will focus on changes in living situations, educational or employment opportunities, peer networks, personal and financial goal achievement, and experiences with GI and the multilevel supports. The third interview will also provide a critical understanding of experiences after GI has ended. Interviews will query about involvement in all financial capability programs, involvement in community building, and access to physical and mental health services. The 90-min interviews are conducted by trained qualitative researchers, digitally recorded and transcribed.

### Retention

Participants who do not respond to two sequential check-ins, or have been out-of-touch with the project for 3 months, will receive a personal phone call from project staff to strengthen participant engagement, check how they are doing, and refer to any needed services. Staff will attempt three calls, texts, or emails within a week prior to reaching out to alternate participant contacts, including family, friends, or agency contacts whose name the participant provided at the enrollment visit. Alternate contacts are asked for updated contact information if the participant’s number has changed and to let the participant know we are trying to reach them. We also attempt to contact the participant through social media if the participant provided their username. If no contact is made, we wait 1 month and try again, including alternate contacts. We track all communications, including SMS sent and received, and retention calls, through our REDCap software platform. Because mobility may be an issue in this population, non-response will not be considered tacit refusal in perpetuity. Non-responsive participants will only be considered “lost to follow-up” at the conclusion of the study (or if they request to be removed from study participation). Participants provide multiple forms of contact info (phone, social media, family/friend contact info, agency contacts) to facilitate communication and connection with the project.

### Ethics

This study, consent forms, and all study procedures have been approved by the University of California, San Francisco Institutional Review Board (IRB #:21–35420). All participants undergo consent to participate in the study, including provision of personal contact information. Participants’ personal information is recorded and stored privately on a secure, password-protected online server. Investigators, project staff, and authorized personnel (i.e., representatives of the sponsoring agency, implementing academic institutions) may review data for monitoring the project. De-identified data may be shared with other researchers for future studies upon reasonable request; personal or potentially identifying information will not be shared. The principal investigators have no competing interests. Any protocol amendments, including outcomes or analyzes, are subject to IRB approval and will be updated in the U.S. National Library of Medicine clinical study registry (ClinicalTrials.gov). Participants will be informed of protocol amendments if terms of participation are affected.

Safety oversight is under the direction of a Data and Safety Monitoring Board (DSMB) composed of three independent investigators with appropriate expertise, including public health, epidemiology, adolescent psychology, cash transfer programming, and health economics. The DSMB met prior to study start, at 6 months into recruitment, will meet again after 1 year of programming, and at least annually thereafter to assess safety data. The DSMB operates under the rules of an approved charter. All serious or unexpected adverse events that are possibly related to study participation will be assessed by the principal investigators immediately upon report and are reported to the UCSF IRB and DSMB within 5 working days of UCSF PI awareness. The DSMB may suggest that the study be modified but will not stop the study. Discontinuing the study would deny enrolled participants the full amount of anticipated GI (for the waitlist group), which is unethical and could inflict harm on participants.

Standard operating procedures (SOP) for distress have been developed and study staff have been trained to address participants’ reports of suicidality, mental distress, or abuse. On surveys and check-ins, reports of suicidality, mental distress, or unsafe relationships trigger an automated alert to the study staff. Participants may also directly report these events to study staff in qualitative interviews, mentoring, or peer discussion groups. Staff contact participants when alerts are received to assess the situation and precede according to protocol. Depending on the participant’s stability and request, staff may contact an on-call clinician to speak to the participant, may refer the participant to services, or may agree to a follow-up call at a later date. All events and staff responses will be recorded for study monitoring.

### Measures

#### Exposure

The primary exposure is intervention arm assignment (see all measure in Table 1). Secondary exposure variables include: receipt of financial mentoring (yes/no) and participation in peer discussion groups (yes/no) during each 3-month study interval. Because engagement with any treatment option will vary by individual, we will also capture intervention dose (e.g., mentoring sessions attended) on study monitoring forms.

**Table 1 tab1:** Study measures: domains, instruments, and time points.

Domain	Instrument/measure	Data source and frequency
Primary exposure		
Intervention	Randomization arm (GI receipt in phase I or phase II)	Study records
Primary outcomes		
Financial well-being	Investments in future (Enrollment in education/training)	Quarterly surveys
Mental Health	CESDR-10: major or probable major depressive episode (64, 65)	Quarterly surveys
Unmet need for health services	Unmet need for mental health services	Quarterly surveys and monthly brief check-ins
	Unmet need for sexual and reproductive health services	Quarterly surveys and monthly brief check-ins
Secondary outcomes		
Financial well-being	Savings, Debt	Surveys at baseline, 6, 12, 18, 24 months
	Credit score	Assessed at baseline, 6, and 12 months
	Financial Capability (knowledge, skills, practices, mindset) (45)	Every six months: baseline, 6, 12, 18, 24 months
Mental health	Anxiety – moderate–severe: score ≥ 10 on GAD-7 (66, 67)	Quarterly surveys
	Hope/ future orientation (68, 69)	Surveys at baseline, 6, 12, 18, 24 months
Physical health	General health (70); fatigue	Surveys at baseline, 6, 12, 18, 24 months
Secondary exposure		
Intervention dose	Engagement with optional intervention components (peer groups and mentoring)	Study monitoring forms
Covariates/Mediators		
Demographics	Age, gender identity, housing/living situation, household membership, income, employment	Quarterly surveys
Strengths and assets	Resilience (71); self-esteem; Black identity (72); decision-making and goal-setting	Frequency varies – six-month and annual surveys
Social and structural contextual factors	Experienced discrimination (73); alcohol and substance use (74); social support (75, 76); social cohesion (77, 78); incarceration; relationship violence (79); trauma (80); prosocial involvement; food security	Frequency varies - quarterly; six-months; and annual surveys

#### Primary outcomes

Financial well-being: We measure investments in the future, specifically by measuring participants’ enrollment in formal education, leadership, or employment training programs during each 3-month study interval. This indicator of wealth generating investments in the future has been utilized in United States studies (34) and represents potential long-term gains, despite the intervention being time-limited. We also collect data on the names of programs, time spent on these activities, the duration enrolled, as well as engagement in informal or self-directed learning. This outcome is an intentional acknowledgement of the agency, assets and resilience of BEA, rather than simply focusing on deficits or vulnerabilities.

#### Mental health

We assess major or probable major depressive episode in the past week at each 3-month study interval using the Center for Epidemiologic Studies Depression Scale Revised (CESDR-10). This measure uses an algorithm that accounts for both symptom severity and duration to determine occurrence or probable occurrence of a major depressive episode and has been validated in young people (64, 65).

#### Unmet health service needs

Defined as the absence of care seeking when needed, unmet mental health (MH) need will be assessed by indication of major or probable major depressive episode on the CESDR-10 or moderate or severe anxiety (score of ≥10) measured by the Generalized Anxiety Disorder 7-item scale (GAD-7) (66, 67) and not reporting that care was utilized in the past 30 days. Service utilization is based on self-report as stating “no” to having accessed any MH service from any kind of health professional (e.g., mental health specialist, general practitioner, nurse, psychiatrist, psychologist, counselor, or social worker) in either an individual or group therapy format. We will assess unmet need for SRH services, which will be measured as self-reported need for SRH (having symptoms of a sexually transmitted infection, unprotected sex, or being at risk of unwanted pregnancy) and not reporting that SRH services were utilized in the past 30 days.

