## Methods

### Trial design

The BEEM trial design is mixed methods, comprised of the quantitative randomized controlled crossover trial with a complementary, nested qualitative component including longitudinal semi-structured in-depth-interviews with a subset of participants to explain the processes that drive the results of the intervention (see Figure 1) (51). We aim to determine the impact of GI on three related sets of primary and secondary outcomes: (a) financial well-being (investing in education and training, savings, debt, financial capability); (b) mental health (depressive symptoms, anxiety, hope/future orientation); and (c) utilization of mental health and sexual and reproductive health (SRH) services. For the trial, 300 low-income BEA are randomized 1:1 to receive 12 months of GI either (a) during the first 12 months of follow-up (Phase I) or (b) in the second 12 months of a total of 24 months follow-up (Phase II). Most GI evaluations have used either parallel-group RCT designs, withholding GI from control groups, or rely on quasi-experimental (pre-post) designs. To address equity in the study, we employ a crossover randomized controlled design to ensure all participants in the project receive GI and offer peer discussion and financial mentoring to all participants. This allows us to implement a rigorous study design to draw causal inferences while centering BEA needs. The addition of opt-in financial capability programs allows us to explore whether complimentary supports can enhance GI while simultaneously respecting BEAs’ autonomy to choose when and how to engage with supports. An additional benefit of the crossover design is that it allows us to not only determine the impact of GI alone, but also sustained impacts once GI is concluded, thus addressing an important knowledge gap regarding sustainability in the evidence for GI programs. This protocol is written according to the Standard Protocol Items Recommendations for Interventional Trials (SPIRIT) 2013 statement (52), an international standard for trial protocols.

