### Research hypotheses

Our primary research question is to understand the potential impacts of GI on BEAs investment in their future (education, employment, training), mental health (depressive symptoms), and unmet mental health (MH) and sexual/reproductive health (SRH) service needs. We are also interested in learning if complementary financial supports propel greater impact on health outcomes and understanding to what degree GI impacts dissipate after the transfers end. Thus, our hypotheses are as follows.

*H1*: *GI will improve all outcomes*. Youth receiving GI in phase I will have greater increases in investments in their future (H_1a_), greater decreases in depressive symptoms (H_1b_), and larger reductions in unmet need for MH and SRH services (H_1c_) at 12 months than those who do not received GI in phase I.

*H2*: *GI + financial supports will improve outcomes more than GI alone*. Participants receiving GI in phase I who participate in mentoring or peer discussion groups will have greater increases in investments in their future (H_1a_), greater decreases in depressive symptoms (H_1b_), and larger reductions in unmet need for MH and SRH services (H_1c_) at 12 months than those not opting into financial support programs.

*H3*: *Gains from GI will be sustained*. Participants receiving GI in phase I will not experience a decline in odds of enrollment in educational/training programs (H_3a_) or an increase in odds of depressive symptoms (H_3b_) or unmet need for MH and SRH services (H_3c_) following the removal of GI (between month 12 and 24).

*H4*: *Accessing complementary financial supports prior to receiving GI will improve overall outcomes.* Among BEA who do not receive GI in phase I, those who engage in mentoring or peer discussion groups in phase I will have greater increases in investments in their future (H_4a_), greater decreases in depressive symptoms (H_4b_), and larger reductions in unmet need for MH and SRH services (H_4c_) at 24 months than BEA who did not opt-in into the financial programming prior to receiving GI.

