#### Exploratory mediation and moderation analyses

We will conduct a number of exploratory mediation and moderation analyses. For example, in mediation analyses we will investigate whether covariates, such as food insecurity, or interim financial well-being outcomes, such as debt, credit, or income, measured at 3, 6, and 9 months mediate the relationship between intervention assignment and subsequent mental health outcomes (i.e., less anxiety and depressive symptoms) measured at 6, 9, and 12 months. We will also investigate whether changes in financial and mental health outcomes mediate the relationship between intervention assignment (GI) and reduced unmet service needs. Finally, we will explore whether intervention impacts are different by gender, parenting status, or living situation (moderation).

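### The trial states a service-utilization aim but lists only unmet need, and unmet mental-health need can fall through fewer symptoms with no change in care use

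*Protocol article*

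**What the plan says.** All references are to the protocol article.

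- **Trial design** lists three sets of outcomes on which the effect of guaranteed income (GI) is to be determined. The third is "c) utilization of mental health and sexual and reproductive health (SRH) services".
- **Research hypotheses** frames the same domain as unmet need: H1c predicts "larger reductions in unmet need for MH and SRH services" at 12 months in the arm paid first. H1b concerns depressive symptoms.
- **Table 1** lists two service outcomes, unmet MH need and unmet SRH need. Neither it nor the Secondary outcomes text contains a service-use outcome.
- **Unmet health service needs** defines the MH outcome in two parts. For need, "unmet mental health (MH) need will be assessed by indication of major or probable major depressive episode on the CESDR-10", or by a GAD-7 score of 10 or more. For care, the participant is "not reporting that care was utilized in the past 30 days". Both parts must hold. The SRH outcome has the same structure, with self-reported SRH need as its first part.
- **Mental health** gives the H1b outcome: "We assess major or probable major depressive episode in the past week at each 3-month study interval", using the CESDR-10. GAD-7 of 10 or more is also a secondary outcome.
- **Exploratory mediation and moderation analyses** will examine "whether changes in financial and mental health outcomes mediate the relationship between intervention assignment (GI) and reduced unmet service needs".

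**The concern.** Two problems follow from reading these sections together.

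First, the utilization question has no outcome that answers it. Care use is asked, but it enters the listed outcomes only as one part of unmet need. That composite moves when need moves, when care moves, or when both do. It cannot say which. A real change in care-seeking could also be masked by a change in need in the opposite direction.

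Second, the need part of the MH outcome contains the H1b outcome and a secondary outcome. A participant who stops meeting the symptom criteria leaves the unmet-need group whatever their care use. Results for H1b and for the MH part of H1c are therefore not two separate pieces of evidence. A mediation model with depression or anxiety as mediator and unmet MH need as outcome will find an association that is partly built in by definition.

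At stake is how a positive H1c may be read: as less need, as more care, or as some of each.

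**Working it through.** **Step 1. The plan's own figure.** Sample size estimation gives detectable differences of 4.5–10.6% for unmet need, from 300 participants, 5.7 observations each, alpha 0.05, power 0.80, ICC 0.20–0.80 and a control-arm range of 5–40%. I used the repeated-measures formula for two proportions, where m is participants per arm, n observations per participant, d the difference, and D = 1 + (n − 1) × ICC:

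m = [z_α √(2 p̄ q̄ D) + z_β √(D(p1q1 + p2q2))]² / (n d²)

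With m = 150, n = 5.7 and a two-sided test, detectable decreases run from 3.4 to 13.9 points over that grid. This does not reproduce the stated range. Sidedness is not stated and the 5–40% can be read in more than one way, so I do not call it an error, and the point does not depend on it.

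**Step 2. The composite.** Unmet MH need = P(need) × P(no care | need).

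Inputs:
- P(no care | need) = 58%. The Introduction gives this figure for Black adolescents and young adults with serious mental illness untreated over the past year. Using it for screen-positive need and a 30-day window is an assumption.
- P(need) = 40% without GI and 30% with GI. Both are assumptions.
- Each person's care use is the same whether or not they receive GI.
- People who lose their symptoms are drawn proportionally from those in care and those not in care.
- 10% of people who would have no need in either arm use care. This is also an assumption, and it cancels out.

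| Cell | No GI | GI |
|---|---|---|
| Need, no care (unmet need) | 0.40 × 0.58 = 23.2% | 0.30 × 0.58 = 17.4% |
| Need, care | 0.40 × 0.42 = 16.8% | 0.30 × 0.42 = 12.6% |
| No need, care | 0.60 × 0.10 = 6.0% | 6.0% + 0.10 × 0.42 = 10.2% |
| No need, no care | 54.0% | 59.8% |
| Any care | 16.8 + 6.0 = 22.8% | 12.6 + 10.2 = 22.8% |

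Unmet need falls by 23.2 − 17.4 = 5.8 points. Care use differs by 0.

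**Step 3. Range.** With 40% or 80% of those in need lacking care, the fall is 0.10 × 0.40 = 4.0 or 0.10 × 0.80 = 8.0 points. The proportional-remission assumption also matters. If only people already in care lose their symptoms, unmet need stays at 23.2% although need still falls to 30%.

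**Step 4. Would it be detected?** Effective n per arm = 150 × 5.7 / (1 + 4.7 × ICC). The detectable fall is from the Step 1 formula at a control rate of 23.2%.

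| ICC | Effective n per arm | Detectable fall (80% power) | Power for 23.2% vs 17.4% |
|---|---|---|---|
| 0.2 | 855 / 1.94 = 441 | 7.5 points | 57% |
| 0.5 | 855 / 3.35 = 255 | 9.6 points | 37% |
| 0.8 | 855 / 4.76 = 180 | 11.2 points | 28% |

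A larger symptom effect does more. If need falls by 15 points, unmet need falls by 0.15 × 0.58 = 8.7 points, and power is 91%, 71% and 56%.

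**The case against.** The strongest reply is that the endpoint matches its hypothesis. The abstract, the hypotheses, Table 1 and the primary analysis all name unmet need, and fewer people in need is a true reduction in unmet need. The word utilization appears as an outcome set only in Trial design. The article's Discussion summary promises findings on unmet needs, not on service use. This stands, and it is why unmet need should remain primary. It does not remove the mismatch: the stated utilization aim still has no outcome.

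Several stronger readings are tempting, and the document does not support them.

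- *Unmet need falls automatically when symptoms fall.* It does not if those who improve were already in care (Step 3).
- *H1c merely restates H1b.* H1c also covers SRH, which contains no CESDR-10 or GAD-7 item. The MH outcome also depends on anxiety and on care use. Monthly check-ins are a listed source too, and they ask about service needs; the two scales are listed for quarterly surveys only.
- *A 5.8-point fall exceeds the 4.5% the plan can detect, so a misleading positive is likely.* The 4.5% is the lowest value over a range of assumptions. At a 23.2% control rate, 5.8 points is below the detectable difference at each ICC in Step 4.
- *The mediation plan as a whole is circular.* It also covers financial mediators and SRH need. Only depression or anxiety with unmet MH need overlaps by definition.

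It can also be said that a need-by-care table is detail for an analysis plan. That is fair for the table alone, but not for an aim and an outcome list that disagree within the same article.

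**Conclusion.** The point holds in limited form. The stated utilization aim has no listed outcome, and unmet MH need can fall with no change in care use. Such a fall would support H1c as worded. It would not be evidence on utilization, and it would not be independent of H1b. The overlap with H1b is confined to the MH outcome. The SRH outcome shares the form of need combined with no care, but not the symptom scales. The mediation analysis is circular for one pairing: depression or anxiety with unmet MH need.

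The illustrative size is a 5.8-point fall with zero change in care use, or 4.0 to 8.0 points if 40% to 80% of those in need lack care. It would reach significance in a minority of trials at ICC 0.5 and 0.8, and in a little over half at 0.2. These figures rest on the assumed need rates, on carrying the 58% over to a different population and recall window, on proportional remission, and on a two-sided test. The logical point needs none of them. It needs only that some people whose symptoms resolve were not in care.

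A reader might infer that the trial intends to report a positive H1c as better access to services. The article does not say so. The defect is that nothing listed would answer the utilization question.

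**What to change.** 1. Keep unmet MH and SRH need as primary outcomes.
2. Name any MH service use and any SRH service use in the past 30 days as secondary outcomes, analysed in all randomised participants from the items already asked.
3. Report need and care use by arm, as the four need-by-care cells for MH and for SRH.
4. Base any statement about utilization on the service-use outcomes, and describe a fall in unmet need that comes from lower need as such.
5. In the mediation analysis, drop depression and anxiety as mediators of unmet MH need, or make MH service use the outcome in that model.
6. Do not compare care use only among people who have need after randomisation. GI may change who is in that group, so the comparison would no longer be a randomised one.

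The cost is two secondary outcomes, a short table, and an amendment to the outcome list and registry entry. No new survey item, change of primary outcome or change of sample size is needed. The downside is that a positive H1c may have to be described more modestly.

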#### Primary analyses

Our primary analyses will test the hypothesis that GI will improve all primary outcomes at 12 months (H1). Specifically, we hypothesize that participants receiving GI in phase I will have (a) greater increases in investments in their future; (b) greater decreases in depressive symptoms, and (c) larger reductions in unmet need for MH and SRH services at 12 months than the no-GI arm.

We will use generalized estimating equations (GEE) to test our primary hypotheses and this analysis will follow an intent-to-treat approach by including all randomized participants. Our primary interest is to estimate the marginal or population-average effects of intervention participation on these primary outcomes rather than the effect for a hypothetical average subject (91). Moreover, within-subject outcome correlations are considered nuisance parameters rather than quantities of interest to be modeled explicitly. Accordingly, GEE can be used to estimate the marginal effects using difference-in-differences (DID) comparisons of post-baseline (follow-up) measurements of the Phase 1 GI group with the comparison arm in the main trial Phase. Since our primary outcomes are dichotomous, these models will employ a logit link and assume a binomial distribution. For each model, we will include indicators for study arm, time and the interaction between study arm and time to examine the relative change in outcomes for each arm during Phase 1. If changes in each outcome do not follow a linear trend, we will explore alternative relationships including polynomial and spline terms. Alpha (α) will be set at 0.05 for each of our planned comparisons. Any additional post-hoc comparisons (e.g., paired comparisons of groups at each time point) will maintain a nominal alpha of 0.05 through the use of simulation-based stepdown multiple comparison methods (92).

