#### Sample size estimation

Power analyzes were generated using the equation defined by Diggle et al. (97) to compute minimum detectable effect sizes for the primary analyses to address Hypotheses 1a-1c. The study will begin with 300 participants equally allocated to two study groups. Assuming 25% attrition over 12 months, we anticipate an average of 4.3 observations from 300 participants will be available for analysis of investments in the future and mental health outcomes and an average of 5.7 observations for analysis of unmet service need outcomes. Assuming *α* = 0.05 and power = 0.80, with four highly correlated post-baseline measurements [intraclass correlation (ICC) = 0.20–0.80] and a range of outcomes for waitlist control participants (change in each outcome between 5 and 40%), we will have sufficient power to detect differences as low as 5.7–10.7% for increase in enrollment in educational or training programs and decrease in depression, and 4.5–10.6% for decrease in unmet service need, respectively, in the intervention arm compared to waitlist controls.

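### Unmet mental-health need is defined by two quarterly scales, yet Table 1 and the power calculation also draw on monthly check-ins that, as documented, cannot score it

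*Protocol article*

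**What the plan says.** Under Unmet health service needs, the protocol article sets two conditions for unmet mental-health (MH) need. The first is a positive screen: "unmet mental health (MH) need will be assessed by indication of major or probable major depressive episode on the CESDR-10", or a GAD-7 score of 10 or more. The second is that no care was reported in the past 30 days. The Mental health section places the CESDR-10 at each three-month interval, and Table 1 lists both the CESDR-10 and the GAD-7 under quarterly surveys alone.

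For unmet need, both MH and SRH, Table 1 gives a different source: "Quarterly surveys and monthly brief check-ins". The Monthly check-ins section says the prompts "will query employment, earnings, and service needs for psychological counseling or SRH". Neither scale is mentioned there.

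Sample size estimation starts from 300 participants in two equal groups. It continues: "Assuming 25% attrition over 12 months", "we anticipate an average of 4.3 observations from 300 participants" for enrollment and depression, but "an average of 5.7 observations for analysis of unmet service need outcomes". The detectable differences that follow are 5.7–10.7% for enrollment and depression and 4.5–10.6% for unmet need. MH and SRH share the second range.

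**The concern.** A repeated binary outcome in a GEE needs one definition at every occasion. Between surveys the documented check-in asks about a need for counseling. That is perceived need, which is a different thing from a positive CESDR-10 or GAD-7 screen. If check-in answers entered the model for unmet MH need, the month of measurement would decide what need means. If they did not enter, the Table 1 row and the 5.7 observations would be wrong for this outcome. Either way the text does not agree with itself.

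What is at stake is mainly the meaning of hypothesis H1c for mental health. The choice of data source should be settled before outcome data are examined. The stated detectable difference is a lesser matter.

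**Working it through.** **Inputs**
- Surveys from baseline through month 12: months 0, 3, 6, 9 and 12, so five (Structured surveys; Table 1).
- Check-ins: monthly (Monthly check-ins).
- From Sample size estimation: attrition 25% over 12 months, 150 per arm, power 0.80, ICC 0.20–0.80, and a control range of 5–40%.
- From Primary analyses: alpha "will be set at 0.05 for each of our planned comparisons".
- Assumptions made here: two-sided testing (sidedness is not stated), and the 5–40% range read as the control proportion (the article words it as a change).

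**Step 1. Observation counts**
- Five surveys, linear attrition: 1 + 0.9375 + 0.875 + 0.8125 + 0.75 = 4.375.
- Five surveys, geometric attrition: sum of 0.75^(k/4) for k = 0 to 4 = 4.35.
- Both are close to the plan's 4.3 for enrollment and depression.
- With no attrition at all, five surveys give 5.0. Since 5.7 is larger than 5.0, it cannot come from surveys alone.
- Baseline plus 12 monthly contacts, linear attrition: 1 + sum of (1 − 0.25k/12) for k = 1 to 12 = 11.375 (geometric: 11.30).
- So 5.7 lies between the survey-only count and the full monthly count. The excess over the survey figure is 5.7 − 4.3 = 1.4 observations, or 1.4/5.7 ≈ 25%.

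**Step 2. Can those extra observations be scored?**
- Required by the definition: a CESDR-10 or GAD-7 result, plus 30-day care use.
- Scheduled off-quarter: neither scale.
- As documented, the MH outcome cannot be derived from a check-in. The missing scales settle this without any assumption about a care-use item.

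**Step 3. Effect on the detectable difference**
The repeated-measures formula for two proportions, with n observations per person and m per arm, is

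m = [z(0.975)·√(2·p̄·q̄) + z(0.80)·√(p1q1 + p2q2)]² × (1 + (n − 1)·ICC) / (n·d²), solved for d.

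With m = 150, control 5–40% and ICC 0.2–0.8:

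| n | Plan states | Computed, increase | Computed, decrease |
|---|---|---|---|
| 4.3 | 5.7–10.7% | 5.3–14.8% | 3.5–14.0% |
| 5.7 | 4.5–10.6% | 5.0–14.7% | 3.4–13.9% |

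The plan's ranges do not reproduce under this reading. The upper ends 10.7 and 10.6 match, among other combinations, a 10% control rate with ICC 0.8 for an increase. No single control rate and ICC gave both lower ends.

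Moving from n = 5.7 to n = 4.3 raises d by 0.07 to 0.61 points for an increase and 0.02 to 0.57 points for a decrease. The largest change is at a 40% control rate with ICC 0.2.

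**Step 4. Does the observation count explain 4.5% against 5.7%?**
- At ICC 0.2 the factor (1 + (n − 1)·ICC)/n is 1.66/4.3 = 0.386 for n = 4.3 and 1.94/5.7 = 0.340 for n = 5.7.
- d scales roughly with the square root: √(0.340/0.386) = 0.939.
- 5.7% × 0.939 ≈ 5.35%, not 4.5%.
- Reaching 4.5% for an increase at a 5% control rate, ICC 0.2 and m = 150 would take about 9 observations.

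**The case against.** The strongest reply is that the text already points to quarterly measurement. The abstract and Structured surveys describe outcome collection every three months. The check-ins are presented as serving engagement, retention and referral. Nothing says that perceived-need answers will replace the scales, and H1 is stated at 12 months, when a full survey is given. On this view all that remains is a table cell and one power input. Much of this stands, and it limits the severity. It does not remove the conflict, because the table cell and the power input both concern a primary outcome and both contradict its definition.

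A reader might infer four stronger points that the documents do not support.

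- **That check-ins omit care use.** The content description is one sentence and is not complete: the Ethics section shows that check-ins also pick up suicidality, mental distress and unsafe relationships. A 30-day recall window would suit a monthly prompt. Only the absence of the two scales is firm.
- **That SRH fails in the same way.** SRH need is self-reported with no scale, and the check-ins do ask about SRH service need, so the argument does not carry over.
- **That eight of the twelve monthly points would be unscorable data in the analysis.** This assumes every monthly contact is analysed, which would give about 11.4 observations, not 5.7.
- **That 5.7 is an arithmetic error.** It would fit about half of monthly contacts being answered (11.375/2 = 5.69). The derivation is not shown, and a condensed article may leave it out.

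**Conclusion.** The point holds for unmet mental-health need. Its definition depends on scales given only at the quarterly surveys, while Table 1 and the 5.7 observations bring in check-ins that, as documented, cannot be scored under it. This rests on the schedules in Table 1 and the Mental health section, and on five surveys through month 12.

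The numerical consequence is small: about 1.4 fewer observations per person, and at most about 0.6 percentage points on the detectable difference under the assumptions above. It would be tempting to blame the check-ins for the gap between 4.5% and 5.7%, but the observation count does not explain that gap. Nor is the failure to reproduce the ranges proof of a mistake, since sidedness and the meaning of the control range are ambiguous. The sample size is fixed at 300 and only detectable differences are reported, so the trial's size does not depend on the 5.7. Severity is minor to moderate, and the weight lies on the outcome definition rather than on power.

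**What to change.** - State that unmet mental-health need is derived from the quarterly surveys only, and remove the check-ins from its row in Table 1.
- In Sample size estimation, replace 5.7 with about 4.3 observations for this outcome, give the matching detectable difference, and report it separately from SRH.
- For SRH, keep the check-ins as a source if they also ask about service use in the past 30 days, and show how its observation count was obtained. Otherwise use the quarterly surveys there too.

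The cost is a text correction and a slightly less favorable stated detectable difference for unmet mental-health need. Data collection does not change, and the check-ins keep their referral and retention role.
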